#### Exercise protocol

Individuals assigned to the exercise groups participate in supervised training (3 x per week at 55–65% VO_2_ peak for 45–50 min) for 16 weeks in the Wellness Center of the institution. Each exercise session begins with a 3–5 min warm-up at a low intensity and static flexibility exercises. Participants build up their exercise tolerance to complete 45–50 min of moderate intensity continuous aerobic exercise using a combination of exercise apparati, depending upon their preference. The heart rates that corresponded to 55–65% of measured VO_2_ peak from the exercise test are used to monitor exercise intensity along with perceived exertion to make sure that subjects are working within a safe, but effective range. At the completion of each workout, subjects are taken through a cool-down procedure involving static stretching. Blood pressure is assessed before and after all exercise sessions and if these values are abnormal for the individual, they are not allowed to exercise on that day. Blood glucose is assessed in persons with diabetes prior to and after each exercise training session. If the pre-exercise value is less than 100 mg/dl the individual is given a drink containing approximately 15 g of carbohydrate. However, if the baseline plasma glucose level exceeds 250–300 mg/dl with ketones present, the individual is not permitted to exercise on that day in compliance with ACSM guidelines [18].

### Outcomes

**The primary outcomes** of this study are systemic markers of inflammation**:** CRP,TNFα, IL-6, IL-10, MCP1, markers of oxidative stress, MDA, 8-isoprostanes F2a, uremic toxins, PCS and IS and the faecal microbiota composition. All biochemical markers will be assayed by well-established labs that are blinded to the group assignments of the participants.

**Secondary outcomes** include indices of vascular function; carotid-femoral arterial stiffness as pulse wave velocity (PWV)**,** resting peripheral and central SBP/DBP (measured by applanation tonometry), endothelin-1, and nitrate/nitrite.

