### Statistical analyses

An Intention-To-Treat design will be used in this study. Effects of treatment on all dependent variables will be assessed by a 2 (prebiotic supplement or control) by 2 (aerobic exercise or control) by 3 (time) mixed factor ANOVA. The effect of the prebiotic supplement will be determined by examining the prebiotic supplement x time interaction, the effect of exercise will be determined by examining the aerobic exercise x time interaction, and the combined effect of the supplement and exercise will be determined by examining the 3-way supplement x exercise x time interaction. Significant interactions will be explored through simple effects analysis. The main variables of interest are inflammatory markers, particularly IL-6, and IL-10.

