### Sample size estimates

A study investigating the effects of aerobic exercise on inflammation reduction [24] demonstrated effect sizes (Cohen’s *d*) varying between .40 and .77 for IL-6 and IL-10 and their ratio, which would be considered a medium to large effect. Few studies have investigated the effect of prebiotic supplements on inflammation, though similar magnitude effect sizes were reported for a prebiotic supplement intervention on changes in free circulating uremic solutes indoxyl sulfate and p-cresol sulfate, key indicators of adverse outcomes of CKD [9], though those changes were not found to be significant in that small sample study. Based on these studies, we anticipate medium effect sizes, and with power set at .80, and alpha set at .05, a sample size of 60 (15 per group) is predicted to be sufficient for detecting significant two-way interactions specified in the statistical analysis section. To account for any dropouts from the protocol, missing data will be addressed through multiple imputation, and results of all analyses averaged over multiple imputed datasets. All variables in the analysis will be examined for assumptions for all statistical tests. Data will also be examined in a per-protocol analysis, using only data from participants in all groups who completed 70% or more of their assigned exercise sessions and/or supplement use and who provided outcome data on the relevant variables.

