## Discussion

The purpose of the study is to examine the effect that 16 weeks of supplementation with the prebiotic, RS-2, has on the composition of the microbiota of a sample of stage 3–4 CKD patients. In addition, we will be monitoring the impact of this prebiotic on the levels of key uremic toxins (PCS & IS), markers of inflammation (CRP, TNF-a, IL6,IL10, MCP1), oxidative stress (MDA and 8-isoprostanes F2a,) and some cardiovascular parameters (arterial stiffness and blood pressure) that are known to impact upon the development of CVD. The potential additive effect of 16 weeks of moderate intensity aerobic exercise on the aforementioned variables will also be explored. Since many of the previous studies performed with RS-2 supplementation have been completed with ESRD patients, this study is one of the first to examine the impact of this supplement on the most prevalent stages of kidney disease, stage 3 & 4 [1].

The success of this protocol depends upon the adherence to two behavioral interventions, namely nutritional supplementation with RS-2 and aerobic exercise training for those randomized to the exercise groups. To enhance compliance to the nutritional aspects of the study, all participants have individual counseling sessions with the study dietitian to review various strategies to consume the product. At two-week intervals during the study, a research assistant is tasked with attempting to contact the participants to determine if there are any concerns with taking the supplement. If there are any such issues, the registered dietitian is informed and the issue is addressed with the participant as soon as it is feasible.

The inclusion of supervised exercise training is a strength of the study [25]. There is some evidence that exercise training alone has a favorable effect on the composition and function of the microbiota in some individuals [26, 27]. This information has not been previously examined in persons with CKD who are known to have a dysfunctional microbiota [28, 29]. Having participants directly supervised during each training session ensures that participants are given the guidance that they need to successfully complete their prescribed exercise training [25]. This also builds in a sense of accountability.

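### The protocol lists ten co-equal primary outcomes and points to different main targets in different sections, so it does not fix which outcome decides the trial

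*Protocol article*

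**What the plan says.** - **Outcomes** lists as primary: "CRP,TNFα, IL-6, IL-10, MCP1, markers of oxidative stress, MDA, 8-isoprostanes F2a, uremic toxins, PCS and IS and the faecal microbiota composition". That is nine biomarkers and one microbiota outcome, with no order among them.
- **Background** agrees with this list: its primary aim covers inflammation, oxidative stress, uremic toxins and gut microbiota together.
- **Statistical analyses** applies one ANOVA to every dependent variable and then narrows the focus: "The main variables of interest are inflammatory markers, particularly IL-6, and IL-10".
- **Discussion** describes the purpose as the effect that RS-2 "has on the composition of the microbiota of a sample of stage 3–4 CKD patients". Toxins, inflammation, oxidative stress and cardiovascular measures come in the next sentence as additional monitoring.
- **Sample size estimates** contains the only significance level in the document: "with power set at .80, and alpha set at .05, a sample size of 60 (15 per group) is predicted to be sufficient". The effect sizes cited there are "varying between .40 and .77 for IL-6 and IL-10 and their ratio", taken from a study of aerobic exercise.
- **Analysis of stool samples** gives the microbiota outcome several measures and tests: three alpha-diversity indices, two UniFrac variants and Bray-Curtis, PERMANOVA, MetaLonDA, GEE and a within-arm permutation ANOVA. None is named as decisive.
- **Update** drops exercise, makes the comparison involving exercise exploratory, and replaces the three-factor model with a 2 (supplement) by 3 (time) ANOVA. It does not revisit the primary list or the significance level.

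**The concern.** A protocol has to let a reader say, before the data are seen, which result will count as the trial's answer. Here three sections answer differently: all four domains, IL-6 and IL-10 in particular, or microbiota composition. An analysis plan built on this text would have to choose which section to follow.

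The stake is the error rate behind a claim that RS-2 improved the primary outcome. With ten candidates and no stated rule for success, a significant result on any of them could be presented as a primary finding. The 5% level would then describe each single test but not the claim.

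**Working it through.** **1. The plan's own figure.** The stated total is 60, for 80% power at alpha .05 to detect two-way interactions, where "we anticipate medium effect sizes". The document gives no numerical effect size for this calculation, no correlation between visits and no sphericity value, so 60 can be neither confirmed nor refuted.
- Simple two-group comparison (normal approximation), n per arm = 2(1.96 + 0.84)²/d². For d = 0.5 this is 63 per arm, 126 in total; for d = .40, 198 in total; for d = .77, 54 in total.
- Repeated-measures interaction with f = .25, three visits, visit correlation .5 and epsilon 1: 28 in total.
- Values near 60 appear only for chosen inputs, for example f = .25, correlation .3 and epsilon .5, which gives 61.

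The sample-size paragraph therefore does not settle which outcome was meant to decide. Its inflammatory effect sizes are for IL-6, IL-10 and their ratio. Its prebiotic evidence concerns indoxyl sulfate and p-cresol sulfate.

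**2. Inputs for the error rate.**
- Number of primary outcomes: 10 (Outcomes).
- Contrasts of interest per outcome: 1, the supplement effect (Update).
- Test level: .05, taken from Sample size estimates, because the analysis sections state none.
- Success rule: any one significant primary. This is an assumption; the document neither states nor excludes it.
- Correlation between test statistics: not given; a range is assumed.

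**3. Independent tests.** P(at least one false positive) = 1 − (1 − .05)^k.
- k = 10: 1 − .95^10 = 1 − .599 = .401.
- k = 9: 1 − .95^9 = 1 − .630 = .370. These are the biomarkers alone. Stool is collected only at baseline and week 16, so the three-time ANOVA fits nine of the ten outcomes.

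**4. Correlated tests.** Simulation of ten equicorrelated standard normal statistics, Z_i = √ρ·W + √(1−ρ)·e_i, with any |Z_i| > 1.96 counted as a false positive:

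| Assumed ρ | At least one false positive |
|---|---|
| 0 | 40% |
| .3 | 35% |
| .5 | 29% |
| .7 | 21% |

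This is roughly four to eight times the nominal 5%. If the microbiota outcome were counted as six tests (15 in all, an illustration), independence would give 1 − .95^15 = .537.

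**5. What narrowing does.**
- One outcome at .05: error 5%.
- Two outcomes at .025 each: 1 − .975² = .049. Holm also keeps the overall rate at or below .05.
- All ten at .005 (Bonferroni): 1 − .995^10 = .049.

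Power for a two-group comparison, 30 v 30, assumed d = 0.5: Φ(0.5·√15 − z), with 0.5·√15 = 1.936.
- alpha .05: Φ(1.936 − 1.960) = 49%.
- alpha .025: Φ(1.936 − 2.241) = 38%.
- alpha .005: Φ(1.936 − 2.807) = 19%.

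Power for the group-by-time interaction, N = 60, two groups, three visits, assumed f = .25, epsilon 1, λ = 60·3·f²/(1−ρ), where ρ is here the correlation between visits:
- ρ = .5 (λ = 22.5): 99%, 98% and 93% at the same three levels.
- ρ = 0 (λ = 11.25): 85%, 77% and 57%.

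In all three settings, naming two outcomes costs less power per outcome than adjusting across all ten.

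**The case against.** The strongest reply is that this is a condensed article and that a multiplicity procedure may sit in an analysis plan not shown. That stands: the absence of an adjustment is not, by itself, a finding. It does not answer the disagreement between Outcomes, Statistical analyses and Discussion, which is in the document itself.

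Second, the text is not without emphasis. Statistical analyses singles out IL-6 and IL-10, and the sample-size paragraph cites effects for them. That is fair, but the emphasis is informal, is not carried into Outcomes, and is at odds with the Discussion. The Discussion is narrative, so wording can resolve the conflict.

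Third, a reader might infer more than the document supports:
- *That each primary is tested at .05 and any one success suffices.* Neither is written. The level comes from the sample-size paragraph and the success rule is an assumption, so the error rates are conditional on both.
- *That a false-positive primary is likely.* For the current single contrast the figures run from 21% to 40%, all below one half, and the top value needs independence, which is implausible for related markers measured in the same plasma.
- *That the three interactions per outcome in Statistical analyses all count.* This would raise the rate well above one half, but the Update has superseded that plan for confirmatory purposes.
- *That the most extreme result will become the headline.* This is speculation about reporting; the dissemination policy commits to seeking publication whatever the outcome.

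**Conclusion.** The point holds as an internal inconsistency with a conditional consequence. Ten outcomes are co-equal primaries in one section, while other sections direct attention to IL-6 and IL-10 or to microbiota composition, and the Update left this unresolved. The document does not fix what decides the trial. Under the two assumptions stated (level .05 per outcome, any one significant result read as success), the chance of at least one false-positive primary on the supplement contrast is about 40% with independent tests and about 21% at a correlation of .7. The correlations are assumed. This should be fixed before unblinding. It does not make the trial unsound, because a change of wording made in time resolves it.

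**What to change.** Before unblinding, reconcile Background, Outcomes, Statistical analyses and Discussion by naming one or two confirmatory outcomes.

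- **Which outcomes.** The plan's own emphasis points to IL-6 and IL-10. The investigators should confirm this rather than have it assumed, because the cited IL-6 and IL-10 effect sizes come from an exercise study and exercise has been dropped.
- **Test.** Use the supplement-by-time interaction from the 2 by 3 ANOVA in the Update, at two-sided .05 if one outcome is named, or with Holm at an overall two-sided .05 if two are named.
- **The rest.** Make the remaining biomarkers and all microbiota measures secondary, with no confirmatory claim.

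The cost is wording, with no extra data. If two outcomes are named, the first Holm step is at .025, and the power loss per outcome is not always small: about 49% to 38% for an assumed d = 0.5 with 30 v 30. It is smaller under the repeated-measures interaction (99% to 98%, or 85% to 77%, for assumed visit correlations of .5 and 0). Naming a single outcome avoids the loss.

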### Statistical analyses

An Intention-To-Treat design will be used in this study. Effects of treatment on all dependent variables will be assessed by a 2 (prebiotic supplement or control) by 2 (aerobic exercise or control) by 3 (time) mixed factor ANOVA. The effect of the prebiotic supplement will be determined by examining the prebiotic supplement x time interaction, the effect of exercise will be determined by examining the aerobic exercise x time interaction, and the combined effect of the supplement and exercise will be determined by examining the 3-way supplement x exercise x time interaction. Significant interactions will be explored through simple effects analysis. The main variables of interest are inflammatory markers, particularly IL-6, and IL-10.

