**Discussion:**

This study has the potential to yield information about the effect of RS-2 supplementation on key biomarkers believed to impact upon the development of CVD in patients with CKD. We are examining whether there is an additive effect of exercise training and RS-2 supplementation on these key variables.

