The impact of resistant starch, primarily RS-2, has been primarily demonstrated in hemodialysis patients [11]. There have been few, if any, reported studies of the impact of RS-2 in CKD patients not on dialysis on the aforementioned biomarkers. Other forms of prebiotics (e.g. fructans) have been investigated with varying effects [13]. Therefore, the primary aim of this study is the examine the impact of 16 weeks of supplementation with RS-2, in association with aerobic exercise training, in a sample of stage 3–4 CKD patients on markers of inflammation, oxidative stress, uremic toxins and on the composition of the gut microbiota. Our proposal is novel in that it attempts to address one of the root causes of the elevated inflammation in CKD patients (dysfunctional microbiome) and determine whether moderate aerobic exercise training, which has been shown to have anti-inflammatory effects in some studies with CKD patients, has an additive effect along with RS-2 supplementation.

We hypothesize that supplementation with RS-2 will lead to normalization of the composition of the microbiota in our sample of CKD patients and reduce key markers of inflammation, oxidative stress, and uremic toxins. Reductions in these biomarkers will be associated with favorable changes in cardiovascular variables (arterial stiffness, blood pressure and vasoactive substances). We also hypothesize that moderate intensity aerobic training will have an additive anti-inflammatory effect along with the consumption of the resistant starch. The study is being conducted as a double-blind, placebo controlled, parallel arm randomized clinical trial.

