All other aspects of the protocol remain in place. There are no plans to resume the exercise components of this particular study. Additional modification will be needed for the statistical analyses. Given the reduced number of participants completing the exercise portion of the protocol, the intended comparison between the prebiotic and exercise conditions will only be exploratory in nature. The effect of the prebiotic compared to placebo will be examined by a 2 (prebiotic vs. placebo) × 3 (time) mixed factor ANOVA.

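### The combined effect of RS-2 and exercise is to be read from the three-way interaction, which measures departure from additivity and is zero when the additive hypothesis is exactly true (minor; the comparison is now exploratory)

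*Protocol article*

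**What the plan says.** The hypothesis, at the end of the Background, is that "moderate intensity aerobic training will have an additive anti-inflammatory effect along with the consumption of the resistant starch". The Discussion paragraph of the Abstract repeats the aim: "We are examining whether there is an additive effect of exercise training and RS-2 supplementation on these key variables".

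The Statistical analyses section sets up a 2 × 2 × 3 mixed ANOVA and gives each term a job:

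- Supplement: "The effect of the prebiotic supplement will be determined by examining the prebiotic supplement x time interaction".
- Exercise: "the effect of exercise will be determined by examining the aerobic exercise x time interaction".
- Both together: "the combined effect of the supplement and exercise will be determined by examining the 3-way supplement x exercise x time interaction".

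Follow-up is conditional: "Significant interactions will be explored through simple effects analysis".

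The sample size section justifies 60 participants (15 per group) for the two-way interactions only. The Update then removes exercise, says that the comparison involving the exercise conditions "will only be exploratory in nature", notes that the analyses will need further modification, and names a 2 × 3 prebiotic-versus-placebo ANOVA. It names no test for the exploratory exercise comparison.

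**The concern.** Hypothesis and test do not match. An additive effect means that the benefit of exercise comes on top of the benefit of RS-2. The three-way interaction asks something else: whether the change with both treatments differs from the sum of the two separate changes. It detects synergy or antagonism and does not respond to the size of the combined effect.

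Two misreadings follow if the term is taken as the plan describes it. A non-significant result, which exact additivity predicts, could be reported as no combined benefit. A significant result could be reported as a combined effect when the combination is less than additive. The first is the more exposed, because simple effects follow only a significant interaction.

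**Working it through.** **Inputs.** From the protocol: 15 per group, alpha .05, three time points, and cited effect sizes of .40 to .77. Assumed, because the protocol does not give them: SD 1 at each visit, correlation 0.5 between visits, half of the effect present at week 8, and effects of 0.5 and 1.5 SD as further scenarios. With correlation 0.5 the SD of the change is √(2 × (1 − 0.5)) = 1, so raw and change-score SDs coincide.

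**The plan's own figure.** The 60 cannot be reproduced, because a medium effect is given no number and no correlation is stated. At f = .25 a two-way test needs N = 53, 38 or 28 for correlations of 0, .3 or .5. At d = 0.5 in change-score SDs it needs about 126. This does not bear on the point, since the plan claims no power for the three-way term.

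**Step 1, algebra.** Let RS-2 alone change a marker by a, exercise alone by b, both by c, and neither by 0. The three-way contrast is c − a − b + 0.

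- Exactly additive, a = b = −0.5, c = −1.0: −1.0 + 0.5 + 0.5 = 0.
- Exercise adds nothing to RS-2, a = b = c = −1.5: −1.5 + 1.5 + 1.5 = +1.5.

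The contrast is zero in the case hypothesised and large in a case that contradicts it.

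**Step 2, rejection rates.** Simulation of the planned mixed ANOVA (20,000 trials per scenario). The last column is a two-sample t-test on the change to week 16.

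| Truth | Three-way | Supplement × time | Exercise × time | Both vs RS-2 alone |
|---|---|---|---|---|
| Additive, 0.5 SD each | 5.3% | 37.2% | 38.6% | 26.6% |
| Additive, 0.77 SD each | 4.9% | 75.4% | 75.5% | 53.1% |
| Additive, 1.5 SD each | 4.8% | 100% | 100% | 97.6% |
| No added benefit, 0.77 SD (a = b = c) | 23.7% | 24.0% | 24.5% | 5.2% |
| No added benefit, 1.5 SD (a = b = c) | 72.5% | 73.5% | 72.8% | 5.0% |

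Under additivity the three-way test stays at alpha whatever the effect size, while both two-way tests respond. The last two rows show why the two-way tests do not suffice alone: exercise × time averages over the supplement, so it can be significant when exercise adds nothing to RS-2. Only the direct comparison with RS-2 alone stays at about 5% there.

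**Step 3, precision, in change-score SDs at 15 per group.**

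- Exercise or supplement effect averaged over the other factor: SE = √(1/15) = 0.258.
- One group against another: SE = √(2/15) = 0.365; 95% half-width 2.048 × 0.365 = 0.75.
- Three-way contrast: SE = √(4/15) = 0.516, twice the SE of an averaged effect.

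Power for a true departure from additivity is low unless the departure is large. For an assumed 0.5 SD it is 12.3% in the simulated ANOVA, and 15.8% as a single contrast on the change score (noncentrality 0.5/0.516 = 0.968, df 56). For 0.77 and 1.5 SD the ANOVA figures are 23.7% and 72.5%. A null result therefore does not establish additivity either.

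**The case against.** The strongest reply is that the plan already contains tests that respond to the hypothesis. In a factorial trial, effects that add appear in supplement × time and exercise × time, and those are the terms the trial was sized for. This stands. A reader might infer that the plan cannot support its hypothesis at all, and the protocol does not bear that out: two significant two-way terms would count in its favour. What remains is that the plan reserves those terms for the separate effects and sends the combined question to the three-way term.

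Second, a significant interaction leads to simple effects, which would show whether the combination is better or worse than additive. This also stands, so the protocol does not support saying that the conclusion will be wrong in direction. The gap is the non-significant case. Nor does the protocol say that a null term will be reported as no benefit; that is a risk of misreading.

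Third, the protocol does not define additive mathematically and may use the word loosely. If synergy was meant, the three-way term is the right test, but then the hypothesis is misworded and the two sections still need reconciling.

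Fourth, the Update makes the comparison exploratory and announces changes to the analysis. A reader might infer that the three-way test is retained. The text does not say so; it neither keeps nor replaces it. The main 2 × 3 analysis is unaffected.

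**Conclusion.** The point holds as a mismatch between the stated hypothesis and the term chosen to judge the combined effect. Its weight is minor, because the exercise comparison is now exploratory and the main prebiotic analysis does not use this term.

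The zero under additivity is algebra and needs no assumption beyond the scale: it applies to the scale analysed, and effects that add on a log scale, for example, could give a non-zero term on the raw scale. Rejection at about 5% under additivity does not depend on effect size. The other rejection rates rest on the assumed correlation, time course and effect sizes, and on a full 15 per group. The Update reports that fewer participants completed the exercise portion but gives no numbers by group, so precision with fewer than 15 would be worse by an amount that cannot be stated.

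**What to change.** In the text for the exploratory analysis, restricted to participants randomised during the four-arm period:

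1. Judge the additive hypothesis from the supplement × time and exercise × time effects. Alongside them, report with 95% CIs, whether or not the interaction is significant, (RS-2 + exercise) minus (RS-2 alone) and (RS-2 + exercise) minus (placebo + exercise).
2. Label the three-way term as departure from additivity (synergy or antagonism), and do not use its p-value as evidence for or against a combined effect.

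The combination against placebo with usual care may be shown as a description of the total effect. It cannot show that exercise adds to RS-2, because it is non-zero when only one treatment works.

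The cost is about two sentences and no new data. The downside is imprecision: at 15 per group each of these contrasts has a 95% half-width of about 0.75 change-score SD, and more with smaller groups.

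### Simple effects are a poor follow-up to a significant supplement x time interaction: they ignore baseline or lose the randomised comparison, where a baseline-adjusted between-arm contrast would do neither

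*Protocol article*

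**What the plan says.** Under Statistical analyses, the article sets the test that decides the supplement question: "The effect of the prebiotic supplement will be determined by examining the prebiotic supplement x time interaction". It then fixes the next step: "Significant interactions will be explored through simple effects analysis". It does not say which simple effects are meant (arm within visit, or time within arm), and it names no between-arm contrast that uses the baseline value.

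The Update drops the exercise component and changes the model: "The effect of the prebiotic compared to placebo will be examined by a 2" x 3 (arm by time) mixed ANOVA. It also states "All other aspects of the protocol remain in place". The same section says that the statistical analyses will need further modification, but the only changes it gives are the new model and the downgrading of the exercise comparison to exploratory. No new follow-up rule is given.

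Under Sample size estimates: "a sample size of 60 (15 per group) is predicted to be sufficient for detecting significant two-way interactions", on the basis that "we anticipate medium effect sizes, and with power set at .80, and alpha set at .05". The source effect sizes for exercise are given as Cohen's d "varying between .40 and .77 for IL-6 and IL-10 and their ratio". No between-visit correlation is stated.

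**The concern.** The interaction has two numerator degrees of freedom. A significant result says that the arms differ in their course over three visits. It does not say in which direction, by how much or at which visit. For each blood marker, that information comes from the follow-up, so the choice of follow-up matters even though it does not decide significance.

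Neither kind of simple effect serves well:

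- **Arm within visit.** This compares raw levels at one visit. It is a randomised comparison, but it discards each participant's baseline value, which explains part of the week-16 variance. Applied at every visit, it would also include a baseline comparison that is uninformative under randomisation.
- **Time within arm.** This is a before-and-after change in one group. It absorbs any change common to both arms, which is plausible here because all participants receive dietitian counselling.

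The two kinds can easily disagree, with the within-arm change significant and the raw week-16 difference not. The article gives no rule for reporting such a result.

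**Working it through.** **Inputs from the article.** Total 60, 15 per group, equal allocation, hence 60 / 2 = 30 per supplement arm; three visits; alpha 0.05; power 0.80; a medium effect; source d of 0.40 to 0.77.

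**Assumptions.** Two-sided alpha; medium read as d = 0.5 (or f = 0.25); complete data; normal outcomes with SD 1; equal correlation ρ between visits; no true baseline difference; a week-8 effect half of, or equal to, the week-16 effect. The article gives no ρ, so a range is shown.

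**The plan's own figure.** For a within-between interaction, λ = f² · N · m / (1 − ρ), with m = 3 visits and f = 0.25. For 80% power the required total N is:

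| ρ | 0 | 0.3 | 0.5 | 0.7 |
|---|---|---|---|---|
| 2 groups | 53 | 38 | 28 | 18 |
| 4 groups | 76 | 55 | 40 | 26 |

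Sixty is enough under most of these settings, but no setting tried returns 60, so ρ cannot be recovered from the sample size.

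**Power of each week-16 contrast, without selecting on the interaction.** With n = 30 per arm and d = 0.5, the noncentrality is (d / SD) · √(n/2), where:

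- raw week 16: SD = 1
- change from baseline: SD = √(2(1 − ρ))
- baseline-adjusted: SD = √(1 − ρ²)

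Examples: at ρ = 0.3 the standardised effect is 0.5 / 1.183 = 0.42 for change and 0.5 / 0.954 = 0.52 for adjusted. At ρ = 0.8 it is 0.5 / 0.632 = 0.79 and 0.5 / 0.6 = 0.83.

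| ρ | Raw | Change | Baseline-adjusted |
|---|---|---|---|
| 0.3 | 48% | 36% | 51% |
| 0.5 | 48% | 48% | 59% |
| 0.6 | 48% | 57% | 66% |
| 0.7 | 48% | 69% | 76% |
| 0.8 | 48% | 85% | 89% |

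Simulation, which includes the small cost of chance baseline imbalance, gives 47–48% for raw and 50–88% for adjusted. The adjusted contrast is best at every ρ tried. The plain change score is worse than raw below ρ = 0.5 and equal to it at 0.5.

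**Share of significant interactions with no significant raw week-16 arm difference.** Simulated 2 x 3 mixed ANOVA, interaction F on 2 and 116 df, then a t test on week-16 values:

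- d = 0.5, ρ 0.5 to 0.8: about 32–48% when the week-8 effect is half the week-16 effect; 33–51% when an equal week-8 effect is also allowed.
- d = 0.40, ρ 0.3 to 0.8: 33–64%.
- d = 0.77, ρ 0.3 to 0.8: 7–17%.
- Effect set so that the interaction has the planned 80% power: 2–10% at ρ = 0.3, 9–20% at 0.5, 28–44% at 0.7, 46–58% at 0.8.

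Reading medium as d = 0.5, 80% interaction power is reached only at ρ of roughly 0.75 to 0.8, where the share is about one half.

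**Time within the active arm**, same runs, d = 0.5 and ρ 0.5 to 0.8: non-significant in only 0–10% of significant interactions. The within-arm test will therefore usually be significant when the raw arm comparison often is not.

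**The case against.** Several points on the other side have force.

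- **The interaction decides.** Simple effects only explore it, so a non-significant week-16 comparison cannot overturn the planned conclusion. This stands, and it limits the point to estimation and interpretation.
- **Not a different question.** A reader might infer that the raw week-16 difference targets something other than the difference in change. Under randomisation the expected baseline difference is zero, so both have the same expectation. The loss is of precision. Only the within-arm type leaves the randomised comparison, and the article does not say that this type will be used.
- **Selection flatters the change score.** Among significant interactions at d = 0.5 and ρ 0.5 to 0.8, the change contrast misses only 1–19%, but it is a component of the interaction that was selected on. Without selection it has no advantage over raw at ρ = 0.5 and is worse at ρ = 0.3. This stands, and it is why the remedy is baseline adjustment and not a plain change score.
- **The Update is open-ended.** It foresees further changes to the analyses, so the survival of the follow-up rule rests on the absence of any replacement. That is a fair caveat, but nothing in the article withdraws the rule.
- **A condensed article.** Post-hoc detail is often left to an analysis plan. Here, however, the article names a specific method, and the point concerns that method, not an omission.

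**Conclusion.** The point holds in a limited form. The stated follow-up is either less precise than it need be or not a randomised comparison, and it is the step that gives the direction, size and timing of any RS-2 effect. At 30 per arm and d = 0.5, using the baseline value raises power for the week-16 contrast from 47–48% to 50–88% over ρ = 0.3–0.8. The gain is small at the low end and large at the high end.

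A reader might infer that a third to a half of genuine interactions would show no week-16 arm difference whatever the circumstances. The article does not support that: the figure needs d = 0.5 and an assumed ρ of 0.5 to 0.8, covers only the raw arm comparison, and falls to 7–17% at the top of the article's own effect-size range. Nor does the article say that the results will be reported as within-arm findings. It leaves that possible by not saying which simple effects are meant.

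**What to change.** Replace the follow-up sentence under Statistical analyses, and repeat the replacement with the 2 x 3 model in the Update:

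> A significant supplement x time interaction will be followed by between-arm contrasts at week 8 and week 16, adjusted for the baseline value, with 95% confidence intervals; within-arm changes will be descriptive only.

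The cost is one sentence. It needs no new data or participants, and the interaction test is unchanged. The downside is that within-arm p-values are no longer available as evidence.
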